### Design

A mixed methods (qualitative and quantitative methods), multi-centred, non-randomised between subjects, before-and-after design comparing usual care (control) with the intervention (PEGASUS). Randomised Controlled Trials (RCTs) are not necessarily suited for psychosocial research [28]. In this study it is inappropriate to randomize participants since contamination effects between conditions are likely if surgeons must focus some consultations around the patient goals offered by PEGASUS, but revert to usual care in others. In this non-randomised design, the control group comprises consenting patients receiving usual care. On completion of the control group recruitment, the health professionals receive PEGASUS training, prior to intervention group recruitment. Semi-structured interviews will be conducted with a selection of participants and health professionals involved in the PEGASUS intervention condition. Intervention consultations will be recorded (with permission) and assessed against a study-specific checklist to check the fidelity of the intervention.

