### Sites

Data collection will take place at hospital sites (Bristol, Bath, Truro, Winchester, and Cardiff) with comprehensive breast reconstruction services. The researcher will maintain weekly contact with each site, where clinic staff will identify eligible participants, provide study information and give the researcher the details of those who consent to participate.

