### Procedure (see Additional file 1)

Potential participants will be identified by clinic staff at each site from appropriate clinic lists.

At each participating site, the control group will be recruited before recruitment to the intervention condition begins. Staff will be trained in the use of the intervention once control group recruitment has been completed at their site.

Women identified as being eligible for the control (usual care) group will be given the study information sheet together with a consent form and questionnaire booklet and a stamped – return addressed envelope. Clinic staff will provide these materials and be on hand to address any questions from potential participants (and will contact the research team for assistance if there are any questions they are unable to answer).

Women identified as being eligible for the intervention group will be given the study information sheet, and the opportunity to ask questions about the study. Those interested in taking part will be given a consent form and an appointment at which they will complete the PEGASUS intervention - this appointment will be not less than 24 h after they have first been told about the study (exact details will depend on the specific study site).

During the intervention consultation, women who have chosen to take part in this study will have a discussion with the trained PEGASUS coach that will be aimed at clarifying their explicit goals and expectations about reconstructive surgery. Together, the coach and patient will complete the PEGASUS sheet – a single piece of paper which will summarise the conversation and list explicitly what the patient is hoping breast reconstruction will achieve. The participant will then take this PEGASUS sheet into their consultation with the breast reconstruction surgeon, who will have been trained to use the sheet, to encourage a discussion about the woman’s expectations, thereby framing the surgical discussion in terms of what it is that the patient is hoping to achieve.

We will seek consent from women in the intervention condition to record their PEGASUS consultations in order that we can assess the fidelity of the intervention.

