### Analysis

The analyses will be described in detail in a full Statistical Analysis Plan but, in brief, the design permits a robust statistical analysis using a linear mixed model with random intercepts for longitudinal data, a one-way ANCOVA with baseline pre-op measure as a covariate, and t-tests for prior reasoned group comparisons. An adjusted ANCOVA will be used to account for the between-subjects non-equivalent groups design and this will prevent an overestimation of treatment effect due to measurement error. Primary analyses will be performed under multiple imputation using Multiply Imputed Chained Equations (MICE) and repeated on a complete basis. Data validity checks and missing values analysis will be undertaken prior to descriptive and inferential analysis. PEGASUS is intended for use with any surgical group and we will compare delayed with immediate reconstruction patients for any systematic differences in outcome.

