### Timeframe of the study

The trial started on the 1st of July 2015 and will be completed in June 2019.

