## Discussion

This study will establish whether the PEGASUS intervention offers benefits over usual care for women offered the option of breast reconstructive surgery. Since it focuses on each patient’s individual, personal goals, PEGASUS offers a tool to support health professionals who are looking to provide patient-centred individualized care for women facing the choice of whether or not to undergo breast reconstruction of any sort and at any time (as an immediate or delayed procedure). It is not limited to any particular type or timing of reconstructive surgery since it is delivered after a patient has been given information by her surgical team about the particular procedures for which she is deemed to be a suitable candidate. We will collate information about the decisions women make about reconstructive surgery, as well as details of their diagnosis and other treatment in order to describe our sample.

This study does not employ randomization for the reasons outlined above. Instead, we are employing a rigorous design that is best suited to this specific clinical situation.

We plan future research to explore the acceptability and feasibility of the PEGASUS intervention with other patient groups, including adults seeking cosmetic surgical procedures and young people with craniofacial conditions.

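### Adjusting for a reliability-corrected baseline score does not account for non-equivalent phase groups; case-mix covariates should be added and secular change stated as a limitation

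*Protocol article*

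**What the plan says.** The Design section of the protocol article describes a non-randomised comparison of usual care with PEGASUS in successive phases. The Procedure section fixes the order within each hospital: "At each participating site, the control group will be recruited before recruitment to the intervention condition begins". Staff at a site are trained once that site's control recruitment has closed. On the calendar span, the Timeframe section says: "The trial started on the 1st of July 2015 and will be completed in June 2019".

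The Analysis section lists a random-intercept mixed model, "a one-way ANCOVA with baseline pre-op measure as a covariate", and t-tests for contrasts justified in advance. It then says: "An adjusted ANCOVA will be used to account for the between-subjects non-equivalent groups design and this will prevent an overestimation of treatment effect". The sentence ends by limiting that last promise to measurement error. The term adjusted is not defined, and detail is left to a full statistical analysis plan that is not shown.

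Two case-mix variables appear elsewhere in the article. Indication (invasive cancer, DCIS or risk-reducing surgery) is part of the population definition under Sample size. Reconstruction timing appears in the Analysis section: "we will compare delayed with immediate reconstruction patients for any systematic differences in outcome". The Discussion says the study will collate "details of their diagnosis and other treatment in order to describe our sample". Neither variable is named as a covariate for the group comparison.

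**The concern.** The sentence makes two claims: that the adjusted ANCOVA accounts for the groups not being equivalent, and that it prevents overestimation arising from measurement error. The only mechanism offered is measurement error, and the only covariate named is the baseline score.

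The claim about non-equivalence is too strong. Women are assigned by when they attended. The phases may therefore differ in indication, in the share who are immediate or delayed candidates, and in surgical practice over several years. A corrected slope on the baseline score removes only the part of those differences that the baseline score carries.

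The claim about overestimation has a direction that does not follow. The bias from an unreliable baseline takes the sign of the baseline difference, so it can hide a benefit as easily as inflate one.

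The main research question asks whether PEGASUS is effective. If the sentence passes unchanged into the analysis plan, phase differences outside the baseline score would be read as an intervention effect, and the text would say they had been dealt with.

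**Working it through.** **1. The plan's own figure.** Inputs from Power calculations: d = 0.5, 90 per group, two-sided alpha 0.05. Noncentrality = 0.5 × √(90/2) = 3.354 on 178 df. Power is 91.6% by the noncentral t and 91.8% by the normal approximation. The stated figure of at least 90% reproduces and does not depend on this point.

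**2. What the measurement-error correction removes.** With a fallible baseline, ANCOVA leaves a bias of

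slope × (1 − reliability) × baseline difference.

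The documents give none of these inputs, so all are assumed:

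- slope 0.5, reliability 0.8, difference ±0.3 SD: 0.5 × 0.2 × (±0.3) = ±0.03 SD
- slope 0.7, reliability 0.9, difference ±0.2 SD: 0.7 × 0.1 × (±0.2) = ±0.014 SD
- slope 0.7, reliability 0.7, difference ±0.5 SD: 0.7 × 0.3 × (±0.5) = ±0.105 SD

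The range is about 0.01 to 0.11 SD. With a positive slope, the uncorrected estimate is too high if PEGASUS women start higher and too low if they start lower.

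**3. What it leaves.** Let b be the phase difference in SD units that is unrelated to PEGASUS and remains after adjustment. A shift in one case-mix factor contributes up to (change in proportion) × (its effect on outcome), less whatever the baseline score carries. Assumed examples:

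- a 20-point shift in a factor worth 0.5 SD: 0.20 × 0.5 = 0.10 SD
- a 30-point shift in a factor worth 0.8 SD: 0.30 × 0.8 = 0.24 SD

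**4. Effect on the test when PEGASUS does nothing.** SE = √[(2/90)(1 − r²)], where r is the baseline–outcome correlation (assumed) and r = 0 is the unadjusted t-test. This form takes the group baseline means as similar. Rejection probability = 1 − Φ(1.96 − b/SE) + Φ(−1.96 − b/SE).

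Standard errors: r = 0, √(0.02222) = 0.149; r = 0.5, √(0.02222 × 0.75) = 0.129; r = 0.7, √(0.02222 × 0.51) = 0.106.

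| Residual b (SD) | t-test | ANCOVA, r = 0.5 | ANCOVA, r = 0.7 |
|---|---|---|---|
| 0 | 5.0% | 5.0% | 5.0% |
| 0.1 | 10.3% | 12.1% | 15.6% |
| 0.2 | 26.9% | 34.1% | 46.8% |
| 0.3 | 52.1% | 64.2% | 80.5% |

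The exact noncentral t gives 10.2%, 26.6% and 51.7% for the t-test column. For a given residual, baseline adjustment raises the rejection rate because it shortens the standard error and leaves b in place. If part of a phase difference does act through the baseline score, adjustment reduces b first, and the comparison across a row no longer holds b equal.

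**The case against.** The strongest reply is that the article gives its analysis in brief and defers to a full plan. Adjusted is undefined and could cover more covariates, and a covariate list is usually left to the analysis plan. That stands: a reader might infer that the baseline score will be the only covariate, but the text shows only that it is the only one named. For the same reason, the stated purpose of the diagnosis and treatment data does not prove they will go unused in modelling. The point rests on the rationale the article does state, which a later covariate list would not make correct.

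Other stronger readings also fail:

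- **That the plan promises to remove every source of overestimation.** The sentence limits that promise to measurement error. The broader claim is the one about accounting for non-equivalent groups.
- **That site confounds the comparison.** Each site recruits both groups, so site biases the contrast only if the control-to-PEGASUS ratio differs between sites. Nothing says it will.
- **That the trial has a 27% or 52% false-positive rate.** Those figures follow from assumed shifts and would apply to any comparison with the same residual bias. They do not measure what the unnamed covariates would contribute. The t-tests are also not designated as primary.
- **That measurement-error bias is negligible beside case-mix bias.** The assumed ranges overlap: up to 0.11 SD for the former, 0.10 SD for a moderate case-mix shift.
- **That covariates would cure the design.** Within a site, period and group coincide, so no covariate list removes secular change.

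The article is open about the lack of randomisation, gives contamination as its reason, and itself calls the groups non-equivalent. Whether the delayed-versus-immediate comparison should instead be an interaction with group is a separate, secondary question and not part of this point.

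**Conclusion.** The concern holds in limited form. As written, the Analysis section credits a baseline adjustment, apparently one corrected for unreliability, with accounting for non-equivalent groups. It can account only for differences that act through the baseline score. The measurement-error bias it does address has no fixed direction, so describing the benefit as protection against overestimation is also inexact.

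The size cannot be known from the documents. Under assumed residual phase differences of 0.1 to 0.3 SD, the nominal 5% error becomes about 10% to 52% for a t-test and about 12% to 64% for ANCOVA at r = 0.5. These figures show how sensitive the comparison is; they do not predict the trial's result. The conclusion about the sentence itself follows from the design and needs none of these assumptions.

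**What to change.** 1. **Primary model.** Regress the 3-month score on group, baseline score, indication, immediate or delayed candidacy at recruitment, age where recorded, and site. Use only covariates fixed before the PEGASUS session, not the operation later chosen, which the session may influence. Include the same covariates in the imputation model.
2. **t-tests.** Do not base effectiveness conclusions on unadjusted t-tests.
3. **Sentence.** Restate it to say that the correction addresses bias from measurement error in the baseline score, in either direction. Add that secular change is confounded with group within each site and remains a limitation.
4. **Calendar time.** Explore it only as a sensitivity analysis. Sites may switch at different dates, which could give some between-site information under a common-trend assumption, but the interval will be wider.

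Cost: with three indication categories and five named sites, the added terms use 2 + 1 + 1 + 4 = 8 degrees of freedom. With all 180 women contributing, residual df fall from 180 − 3 = 177 to 169. Indication and reconstruction timing are already identified in the article. Candidacy at recruitment and age need checking, because the article does not say they are recorded as analysis variables.

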### Interviews

We will conduct a nested qualitative study that will involve semi-structured interviews with around 32 patients (8 per site; 4 intervention, 4 control) and 20 health professionals (PEGASUS Coaches and surgeons; 5 per site), exploring experiences of PEGASUS (where appropriate), patients’ expectations of reconstruction and if these were met. Patient interviews will be conducted around the 12 month follow up data collection, using Breast-Q scores (high, middle, low) to purposefully sample to ensure interviews are conducted with patients with varying outcomes. Telephone interviews will be conducted if preferred by the patient or health professional, or if face-to-face is not possible. Face-to-face interviews will be conducted at a time and place of the interviewee’s choosing (following standard University protocols for safe lone working). Interview recordings will be transcribed verbatim and subjected to thematic analysis [37]. Findings will be agreed by the research team, with feedback from the advisory group. Participants’ goals and expectations on the PEGASUS forms will be subjected to content analysis.

### Data storage/confidentiality

A data protection document describes the study’s safeguards for the storage and protection of confidential information, both held manually and on computers. This document is guided by the Caldicott principles for handling patient-identifiable information, The UK Data Protection Act (1998) [38] and Good Clinical Practice guidance [39]. All data will be treated as confidential. Only members of the research team who are also members of the breast reconstruction service at the participating sites will examine clinic and medical records in order to identify potential participants. Once consented, the research team based at the university may require access to participants’ medical records in order to collect and check health economic data. Permission to do this will be included on the participant consent form. Audio files (interviews and consultation recordings) and data will be stored on a password protected computer accessible only by the research team. Completed questionnaires and consent forms will be stored separately, in a locked filing cabinet.

### Research governance, safety and the conduct of the study

It was agreed that an independent data monitoring committee was not necessary and interim analyses will not be conducted. A PEGASUS steering group will be set up with an independent chair and members and will meet every 6 months. The steering group will provide advice and supervision of the study and will focus on the progress of the study, approaches to improve adherence, the collection of follow-up data, participant safety and consideration of new information. The management team (consisting of the principle investigator, clinical psychologist, researcher, health economist and statistician) will meet once-a-month to discuss study progress, protocol adherence and amendments for ethical approval. Access to the final dataset will be restricted to members of the study management group.

### Dissemination of research findings

Members of our steering and management groups will provide expert advice on the dissemination of the main outcomes to participants. The findings of this study will be disseminated via publications in peer-reviewed journals. Dissemination of the findings to health professionals and organisations supporting women with breast cancer will be planned and developed with stakeholders throughout the study.

### Study approvals

This study has been approved by the NRES Committee South Central - Berkshire B (reference 15/SC/0331) and the Faculty of Health and Applied Sciences Research Ethics Committee at the University of the West of England, Bristol. All necessary R&D approvals have been granted by the NHS study sites. The study has been accepted on the National Institute for Health Research (NIHR) Clinical Research Network (CRN) Portfolio.

**Research Sponsor:** University of the West of England, Bristol.

### Timeframe of the study

The trial started on the 1st of July 2015 and will be completed in June 2019.

## Discussion

This study will establish whether the PEGASUS intervention offers benefits over usual care for women offered the option of breast reconstructive surgery. Since it focuses on each patient’s individual, personal goals, PEGASUS offers a tool to support health professionals who are looking to provide patient-centred individualized care for women facing the choice of whether or not to undergo breast reconstruction of any sort and at any time (as an immediate or delayed procedure). It is not limited to any particular type or timing of reconstructive surgery since it is delivered after a patient has been given information by her surgical team about the particular procedures for which she is deemed to be a suitable candidate. We will collate information about the decisions women make about reconstructive surgery, as well as details of their diagnosis and other treatment in order to describe our sample.

This study does not employ randomization for the reasons outlined above. Instead, we are employing a rigorous design that is best suited to this specific clinical situation.

We plan future research to explore the acceptability and feasibility of the PEGASUS intervention with other patient groups, including adults seeking cosmetic surgical procedures and young people with craniofacial conditions.

## Abbreviations

ANOVA: Analysis of variance
BR: Breast reconstruction
DCIS: Ductal carcinoma in situ
LEP: Limited English proficiency
MICE: Multiply imputed chained equations
NHS: National Health Service
PEGASUS: Patients’ Expectations and Goals: Assisting Shared Understanding of Surgery
RCT: Randomised controlled trials
SDM: Shared decision making
VAS: Visual analogue scales
